#### Primary and secondary analysis

All data analyses will be conducted based on the principle of intention to treat [22]. Chi square, ANOVA, and Kruskal-Wallis tests will be used for bivariate analysis. For the primary outcomes of emergency health service use, Kaplan-Meier survival curves and log rank statistic will be used to compare intervention and control groups. A Cox proportional hazards regression model will be used to determine the effect of the interventions and adjust for any potential confounding variables. A general linear model approach will be used for multivariable repeated measures analysis of covariance for continuous outcome variables (e.g. measures of functional status, quality of life and psycho-social well-being) to investigate the differences over the four data collection points. Economic data will be collected to enable a comprehensive evaluation of the cost-effectiveness of the interventions when compared to that of usual care. Mean treatment costs differentials between control and intervention groups will be calculated. The patient level data will be used alongside other routinely available data to inform a decision analytic cost-effectiveness model.

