### Study outcomes

#### Primary outcomes

Primary outcomes include emergency health service use (i.e. unplanned readmissions, time to first unplanned readmission, unplanned Emergency Department, General Practitioner and other health service use), and functional ability (Instrumental Activities of Daily Living [23], Index of Activities of Daily Living [24], Walking Impairment Questionnaire [25]).

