#### Secondary outcomes

Secondary outcomes include health-related quality of life (Short Form-12^v2 ^Survey [26]), psychosocial well-being (Geriatric Depression Scale [27], MOS Social Support Survey [28]), satisfaction with health care, and cost effectiveness (i.e., calculating the number of readmissions avoided, estimating time gained by delaying or preventing time to first re-admission, calculating mean treatment cost differentials between control and intervention groups).

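### Time-to-first-event methods are assigned to all the service-use primary outcomes, most of which can recur, and no adjusted count or rate analysis is named for them

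*Protocol article*

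**What the plan says.** The Primary outcomes section gives the service-use outcomes as "unplanned readmissions, time to first unplanned readmission, unplanned Emergency Department, General Practitioner and other health service use". Trial aims lists the same items. Unplanned readmissions and time to first unplanned readmission therefore stand as separate items.

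Primary and secondary analysis assigns one family of methods to this set: "For the primary outcomes of emergency health service use, Kaplan-Meier survival curves and log rank statistic will be used". The adjusted analysis follows: "A Cox proportional hazards regression model will be used to determine the effect of the interventions and adjust for any potential confounding variables". The sentence before these reads "Chi square, ANOVA, and Kruskal-Wallis tests will be used for bivariate analysis" and ties those tests to no outcome. The general linear model in the same paragraph is for continuous outcomes; its examples are functional status, quality of life and well-being, not service use.

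For cost-effectiveness, Secondary outcomes includes "calculating the number of readmissions avoided, estimating time gained by delaying or preventing time to first re-admission", and the analysis section adds "The patient level data will be used alongside other routinely available data to inform a decision analytic cost-effectiveness model". Sample size expects about 25% attrition (20 per group) over six months and gives death as one of the reasons.

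**The concern.** Kaplan-Meier, log-rank and Cox answer one question well: how soon the first unplanned readmission comes. They are assigned here to a plural set of outcomes in which the other items can happen several times to one patient. A hazard ratio for the first event does not say how many readmissions or visits an intervention prevents. Two interventions that delay the first readmission equally can differ in the number of later ones.

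The trial aims to reduce unplanned readmissions, and its economic evaluation needs the number avoided, which is a difference in counts or rates. As written, the only adjusted model that reaches service use does not produce that quantity. A count comparison by the bivariate tests would leave out the adjustment that the Descriptive analysis section promises for baseline differences. It would also treat a patient who left or died early as having had the full 24 weeks at risk.

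**Working it through.** **1. Outcomes against methods**

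| Outcome item (Primary outcomes) | Can recur in 24 weeks? | Fit of Kaplan-Meier, log-rank and Cox in first-event form |
|---|---|---|
| Time to first unplanned readmission | No, by definition | Suitable |
| Unplanned readmissions | Yes | Uses only the first |
| Unplanned ED use | Yes | Uses only the first |
| GP use | Yes | Uses only the first |
| Other health service use | Yes | Uses only the first |

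**2. What else in the plan could cover the recurring items**

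- Chi square, ANOVA and Kruskal-Wallis could compare numbers between groups, but without covariates and without follow-up time.
- The general linear model is for continuous outcomes.
- No count, rate or recurrent-event model is named.

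**3. The plan's own figures**

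The article gives no readmission or visit rate, so there is no figure on this point to reproduce. Its attrition figures are consistent: 20/82 = 24.4%, close to the stated 25%; 82 − 20 = 62; 4 × 82 = 328. The sample size concerns time to readmission only, and nothing below depends on it.

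**4. Illustration: share of events after the first (assumed inputs)**

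Let the number of readmissions over 24 weeks be negative binomial with mean μ and dispersion k.

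- P(at least one event) = 1 − (1 + kμ)^(−1/k)
- Share of events after the first = 1 − P/μ

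The ends of the range:

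- μ = 0.5, k = 0.5: P = 1 − 1.25^(−2) = 0.360; 0.360/0.5 = 0.72; share after the first 28%.
- μ = 1.2, k = 2: P = 1 − 3.4^(−0.5) = 0.458; 0.458/1.2 = 0.38; share after the first 62%.

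In between:

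- μ = 0.8, k = 0.5: P = 1 − 1.4^(−2) = 0.490; share after the first 39%.
- μ = 0.8, k = 2: P = 1 − 2.6^(−0.5) = 0.380; share after the first 53%.

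Outside that range, with k from 0 (Poisson) to 2, the share is 14-30% at μ = 0.3. It is 68-79% at μ = 3, which might describe GP visits.

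**5. Illustration: follow-up time in raw counts (assumed timing)**

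Suppose the expected 25% leave halfway through on average. Mean follow-up is then 1 − 0.25/2 = 0.875 of 24 weeks. With a constant event rate and equal loss in every arm, raw mean counts, and the differences between them, come out at 87.5% of their value for a full 24 weeks under observation. Ratios between arms do not change.

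**The case against.** The strongest case on the other side has four parts.

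*The counts may be analysed anyway.* The bivariate tests come under a heading that covers primary and secondary analysis, and nothing bars them from comparing numbers of events. Nor does the article say that every Cox model stops at the first event. This stands. A reader might infer that repeat readmissions and visits are thrown away altogether; the text does not support that. It supports only that the method assigned to these outcomes, in its standard form, does not use them.

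*Readmissions avoided is planned.* A reader might infer that this quantity will not be estimated. Secondary outcomes says that it will be ("calculating the number of readmissions avoided"), and a decision-analytic model fed by patient-level data is planned as well. What is lacking is a named analysis that would supply an adjusted, follow-up-corrected estimate with its uncertainty.

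*The size is assumed.* The article speaks of use, not of counts, and gives no rates. Reading the items as recurrent is reasonable but is an inference. The share of events after the first is also not the share of information lost, because under overdispersion repeat events cluster in the same patients. A reader might further infer that an arm with heavier loss will falsely appear to use fewer services. Survival methods handle unequal follow-up by censoring, so that risk belongs only to the raw-count tests. The article plans the same loss of 20 in each group, and nothing in it points to differential attrition.

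*The article is condensed.* An analysis plan not shown may name a count model, and its absence here would not by itself be a finding. The point is narrower: the article does state a method for these outcomes, and that method does not fit most of them. A later plan would have to depart from this sentence to put it right.

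**Conclusion.** The point holds as a mismatch between stated method and stated outcomes. Survival methods are assigned to the whole set of service-use primary outcomes, but only one item is explicitly a time to event. The only adjusted model that reaches the recurring items does not, in first-event form, estimate a difference in numbers of readmissions or visits. The available count comparisons are unadjusted and ignore follow-up time.

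The size cannot be fixed from the article. On assumed means of 0.5 to 1.2 readmissions and dispersions of 0.5 to 2, roughly 28-62% of readmissions would lie outside a first-event analysis. The share is smaller at lower rates and larger for frequent contacts such as GP visits. These figures illustrate scale and are not estimates for this trial. The comparison for which the trial is powered, time to readmission, is properly served by log-rank and Cox and is unaffected.

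**What to change.** - State that Kaplan-Meier, log-rank and Cox apply to time to first unplanned readmission.
- For the numbers of unplanned readmissions and of ED, GP and other visits, name negative binomial regression, or an equivalent recurrent-event model, with the log of time alive and under follow-up as offset. Adjust for the same covariates as the Cox model.
- Report rate ratios and rate differences with confidence intervals, and use the readmission rate difference for the readmissions-avoided calculation and the economic model.

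The cost is a change of wording and a little more analysis; no extra participants or visits are needed. It does require an event count and an end-of-follow-up date for each participant. The article does not describe how these are recorded, so their availability should be confirmed.

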#### Sample size

A total of 328 participants (82/group) is aimed to be recruited. Based on our previous research in the area [19] it is anticipated that there will be approximately 25% attrition (20/group) over 6 months of follow-up for reasons such as death, changing mind about participating, or moving away. A sample of 62 completing participants per group (82-20 = 62) is required to detect a 4 week difference in time to hospital readmission. This sample size was determined by power analysis and based on an expected difference in median time to readmission between groups over 24 weeks. Significance level (alpha) was established at 0.05 to avoid a Type 1 error, and power (1 - beta) was set at 90% to avoid a Type II error. Therefore, for a 90% chance of detecting as significant a 4 week difference in time to hospital re-admission, 62 patients in each group are needed to complete the study.

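### The repeated-measures ANCOVA named for the continuous outcomes, if run in its classical form, leaves out anyone with a missing visit; with about 25% attrition expected, this is in tension with intention to treat

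*Protocol article*

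**What the plan says.** In the protocol article, under Primary and secondary analysis, the method for functional status, quality of life and psychosocial well-being is given as: "A general linear model approach will be used for multivariable repeated measures analysis of covariance for continuous outcome variables". Its purpose is "to investigate the differences over the four data collection points", that is baseline and 4, 12 and 24 weeks. The same paragraph states: "All data analyses will be conducted based on the principle of intention to treat"; the section on intervention integrity repeats this. Functional ability, measured by two activities-of-daily-living scales and a walking questionnaire, is listed under Primary outcomes.

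Under Sample size, "it is anticipated that there will be approximately 25% attrition (20/group) over 6 months of follow-up". Death, withdrawal and relocation are the causes given there. The only mention of missing data is under Data quality assurance, where returned questionnaires are checked. The article does not say what happens in the analysis to a participant who misses a visit.

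**The concern.** In the classical repeated-measures general linear model, each participant is one record holding all visits. Without imputation, a record with a gap is dropped whole. Someone with valid 4-week and 12-week scores but no 24-week score then contributes to no time point.

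Participants are older people selected for risk of readmission, and the named reasons for loss include death and withdrawal. Loss related to poor function is therefore plausible. Those remaining in the model could be a healthier subset of those randomised, in an analysis that carries one of the two primary outcome domains and several secondary outcomes. Scores already collected would also go unused.

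This point concerns a method the article names. It does not rest on the absence of detail that an analysis plan would normally hold.

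**Working it through.** **Inputs from the Sample size section.** "A total of 328 participants (82/group) is aimed to be recruited"; attrition about 25%, taken as 20 per group; "A sample of 62 completing participants per group (82-20 = 62) is required to detect a 4 week difference in time to hospital readmission".

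**The plan's own figure.** Forward: 82 × 0.25 = 20.5, taken as 20, and 82 − 20 = 62. Backward: 62 / (1 − 0.25) = 82.7, which rounds up to 83 against 82 stated. The recruitment target reproduces to within one participant per group.

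**Participants left in a complete-case model.** Assume that every participant lost misses at least one visit and that nobody else does:
- per group: 82 − 20 = 62, and 62 / 82 = 75.6%
- in total: 4 × 62 = 248 of 4 × 82 = 328

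Intermittent missed visits would lower this. The article gives neither a rate of missed visits nor the timing of dropout.

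**Precision at an early visit.** The standard error of a group mean is proportional to 1/√n. If nearly all 82 give a 4-week score and 62 are analysed, the ratio is √(82/62) = 1.15. For other losses it is 1/√(1 − loss):

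| Loss | Ratio |
|---|---|
| 20% | 1.12 |
| 24.4% (20/82) | 1.15 |
| 30% | 1.20 |
| 35% | 1.24 |

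As an illustration, a standardised difference of 0.507 has 90% power with 82 per group and about 81% with 62. That comparison applies only at a visit where nearly all 82 have a score.

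**Precision at week 24.** Participants lost by then have no 24-week score under either method. In simulation (82 per group, correlation 0.6 between visits, dropout driven by the 4-week score), moving from the completer analysis to a likelihood analysis changed the sampling SD of the 24-week estimate from 0.1426 to 0.1416 in one setting and from 0.1445 to 0.1436 in another. Since 0.1426/0.1416 = 1.007, the gain is about 1%.

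**Bias.** All settings are assumed (82 per group, correlation 0.6), and effects are in SD units:

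| Dropout depends on | True effect | Completer ANCOVA | Likelihood, all observed scores |
|---|---|---|---|
| 4-week score, 22% lost | 0.40 | 0.392 | 0.404 |
| 4-week score, 26% lost | 0.40 | 0.370 | 0.400 |
| Last observed score, differing by arm | 0.50 | 0.467 | 0.503 |
| Baseline score only, 25–28% lost | 0.40 | 0.399–0.400 | not needed |

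The third row comes from 200 runs, with a Monte Carlo standard error of 0.010. On average 122 of 164 participants were complete and 148 had at least one follow-up score. The completer shortfalls are 0.40 − 0.392 = 0.008, 0.40 − 0.370 = 0.030 and 0.50 − 0.467 = 0.033. The sampling SD of a single estimate is about 0.14, so the largest shortfall is about a quarter of it (0.033/0.14 = 0.24). With baseline as a covariate, dropout driven by baseline alone gave no bias.

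**The case against.** The strongest case on the other side is that deletion is inferred. The article speaks of a general linear model approach; that can follow imputation, or be fitted in long form by likelihood. Nothing restricts the analysis to completers, and missing-data handling often sits in a document that is not shown here. This stands, and it is why the point is conditional on the classical form.

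Four stronger readings are tempting and are not supported:

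- *The method contradicts intention to treat.* Intention to treat at its core means analysis by allocated group. Handling of missing visits is a related but separate choice, so this is a tension.
- *The plan will analyse 62 per group.* The 62 is the completer target for the time-to-readmission calculation. It is used here only as what the stated attrition would leave.
- *All these outcomes become completer analyses.* The article also plans ANOVA and Kruskal-Wallis tests, which can use everyone observed at a given visit.
- *Results at every visit lose 15% in precision and are badly biased.* The 15% belongs to early visits. The simulated bias is small and needs dropout that depends on post-baseline scores, which the article does not establish.

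What remains is that the named method, read in its usual sense, does not convey that incomplete participants are kept. If imputation or a likelihood fit is intended, the text should say so.

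**Conclusion.** The point holds in conditional form. Run classically and without imputation, the named analysis would keep about 62 of 82 per group, or fewer with intermittent gaps, and would set aside scores from participants who did respond at 4 or 12 weeks. That fits poorly with an intention-to-treat commitment for a primary outcome domain.

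The consequences are moderate: a standard error up to about 15% larger at week 4, close to no loss at week 24, and a bias of about 0.01 to 0.03 SD under the assumed dropout patterns. The count assumes that all attrition shows up as missed visits, and the 15% assumes near-complete response at week 4. The Kaplan-Meier and Cox analyses of readmission can censor those lost and are not touched by this.

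**What to change.** Replace the repeated-measures ANCOVA with a likelihood-based linear mixed model for repeated measures:

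- outcomes: the 4-, 12- and 24-week scores
- fixed effects: group, visit, group-by-visit, baseline score and hospital
- covariance: unstructured across visits
- participants: everyone randomised who has at least one follow-up score, analysed in the allocated group
- reporting: the group contrast at each planned visit, since the article ranks none of 4, 12 and 24 weeks above the others

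State that the model assumes data are missing at random given the observed scores. State also that it does not resolve scores after death: it implicitly treats them as values that could have been observed, and death is among the attrition reasons the article names.

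The cost is a few sentences in the analysis section, with the same data and standard software. The article reports that data collection was under way when it was written, so the change could precede analysis. The downside is reliance on missing at random, which is still a weaker assumption than a completer analysis with the same covariates needs. Participants with no follow-up score contribute under neither approach.

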### Publication process

The principal and co-investigators of the grant will be responsible for ensuring the results of the trial, regardless of the outcomes, are published within a reasonable timeframe after conclusion of the trial. The reporting of this trial will adhere to the latest CONSORT [21] statements at the time of manuscript submission.

### Ethical approval

The trial has received ethical approval from the Human Research Ethics Committees of the Mater Health Services (No. 1173A) and Queensland University of Technology (No. 0800000219). The trial will be implemented in compliance with this protocol and the Australian National Statement on Ethical Conduct in Human Research [29].

## Discussion

Acute hospital services comprise the largest section of health expenditure in developed countries. Prevention or delaying of disease is known to produce more effective use of services and determining the optimal transitional care for at-risk patients following a hospital admission has still not been achieved. Lowering the use of acute care services is the most beneficial and significant cost saving expected as a result of positive outcomes from the proposed interventions in this study. This knowledge will permit forward planning and the development and construction of effective health services to meet client needs and prevent emergency readmissions into hospital.

A limited number of long term trials have been undertaken on interventions to prevent emergency health service use and promote health behaviour changes to improve the functional ability, independence and quality of life of older people at high risk of poor outcomes following hospital discharge. Accordingly, current models of discharge planning and follow-up care do not always address their needs. In a recent randomised control trial [19], support was found for the effectiveness of an innovative model of discharge planning and follow-up management of older adults at risk for hospital readmission; however, the trial was unable to examine the optimal components of the multi-faceted intervention on health and economic outcomes. This current trial extends this previous work to determine the comparative effectiveness, as compared to that of receiving usual care, of interventions that deliver 1) in-home and telephone follow-up management with hospital-to-home exercise strategies, 2) exercise strategies only, and 3) in-home and telephone follow-up only. The results will determine effective strategies to reduce readmissions and improve functional status, independence, and psycho-social well-being in this at risk group.
